**Method/Design:**

The trial will employ a randomised 2 x 2 factorial design. Eligible patients will be stratified by anaesthetist and block randomised into one of four groups: Group one will receive preoperative warming with a forced air warming device; group two will receive warmed intraoperative irrigation solutions; group three will receive both preoperative warming and warmed intraoperative irrigation solutions; and group four will receive neither intervention. Participants in all four groups will receive active intraoperative warming with a forced air warming device. The primary outcome measures are postoperative temperature, thermal comfort, and total recovery time. Primary outcomes will undergo a two-way analysis of variance controlling for covariants such as operating room ambient temperature and volume of intraoperative irrigation solution.

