## Method

### Trial design

The trial will employ a randomised 2 x 2 factorial design. An equal ratio of participants will be allocated to each group. This design will enable the study of each intervention on the outcome variable, as well as the effects of interactions between interventions on the outcome variable.

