### Sample size

The trial has been powered to detect a 0.05°C (SD 0.5) difference in temperature between the four study groups. This was deemed a clinically significant difference based on the researchers experience and previous published studies [12,24]. Based on this number, and given the trial’s design, a total sample size of 120 participants is required to power the trial at 80% with a significance level of 5%.

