### Randomisation

A statistician, with no clinical involvement in the trial, will computer-generate a stratified (by anaesthetist) block randomised sequence. This list will remain concealed from the trial coordinator at all times. When the trial coordinator has assessed and enrolled a participant, she will telephone an independent person to obtain the treatment allocation. She will then inform the appropriate nursing and medical staff who will deliver the intervention(s). The trial coordinator will not collect outcome data, deliver the intervention(s), or provide patient care.

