### Statistical analysis

Intention-to-treat analysis will be applied. Data will be analysed according to the 2x2 randomised factorial study design. The two-way analysis of covariance (two-way ANCOVA) will be used for the primary and secondary outcome measures of temperature, thermal comfort and total recovery time. The two-way ANCOVA model will also include operating room ambient temperature, volume of irrigation solution, length of surgery, blood loss and other covariates identified in the bivariate analyses. The analysis will be adjusted for baseline temperature and thermal comfort. Pair-wise comparison between groups will be conducted based on the results obtained from the two-way ANCOVA.

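### Randomisation is stratified by anaesthetist, but the ANCOVA does not pre-specify anaesthetist and leaves its inclusion to a bivariate screen

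*Protocol article*

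**What the plan says.** The Randomisation section has a statistician "computer-generate a stratified (by anaesthetist) block randomised sequence". The abstract agrees: "Eligible patients will be stratified by anaesthetist and block randomised into one of four groups". No other stratification factor is named.

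The Statistical analysis section sets the model: "The two-way analysis of covariance (two-way ANCOVA) will be used for the primary and secondary outcome measures". It then lists the covariates as "operating room ambient temperature, volume of irrigation solution, length of surgery, blood loss and other covariates identified in the bivariate analyses", and adds: "The analysis will be adjusted for baseline temperature and thermal comfort". Six covariates are therefore fixed in advance, four measured around the operation and two at baseline. Anaesthetist is not one of them. The last words of the covariate list leave room for further variables chosen by bivariate screening.

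The Interim analysis section plans an efficacy look at 75% enrolment, which is 0.75 × 120 = 90 participants. The same model question therefore arises twice.

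**The concern.** Blocking within anaesthetist balances the four groups for each anaesthetist. Differences between anaesthetists then largely cancel out of the treatment contrasts. If the model has no anaesthetist term, those differences stay in the residual variance. The standard error it reports is then larger than the true sampling variability of the estimate.

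Whether to adjust for a stratification factor follows from how participants were allocated, so it can be settled before any data are seen. Under the present wording it depends on an observed association. Anaesthetist could be in the model for temperature and out for recovery time, or out at 90 participants and in at 120. What is at stake is calibration and some efficiency: intervals wider than they need be, tests below their nominal level, and a possible gain in power not taken.

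**Working it through.** **The plan's own figure.** The Sample size section says "The trial has been powered to detect a 0.05°C (SD 0.5) difference in temperature between the four study groups" and gives 120 participants for 80% power at 5%. With a two-sided test (sidedness is not stated), a main effect needs 2 × [(1.960 + 0.842) × 0.5 / 0.05]² ≈ 1,570 per arm, or 3,140 in total. So 120 does not follow from 0.05°C. That is a separate problem and this point does not rest on it. To see the effect of the anaesthetist term, the effect size used here is the one that 120 participants detect with 80% power.

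**Inputs from the article.** N = 120 and SD 0.5 (Sample size); "An equal ratio of participants will be allocated to each group" (Trial design), hence 30 per group and 60 v 60 for each main effect.

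**Assumptions.** The share ρ of outcome variance due to anaesthetist, left after the named covariates, is taken as 0, 0.05, 0.10 or 0.20. The article gives neither this share nor the number of anaesthetists nor the block size. The SD of 0.5 is taken as the total SD in the model without anaesthetist.

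**Formulas.**
- SE reported without anaesthetist: 0.5 × √(2/60) = 0.0913
- True SE under stratified blocks: 0.0913 × √(1 − ρ)
- Ratio of the two: 1/√(1 − ρ)
- Type I error without anaesthetist: 2 × [1 − Φ(1.960/√(1 − ρ))]
- Illustrative effect: (1.960 + 0.842) × 0.0913 = 0.256°C
- Power without: Φ[(0.256 − 1.960 × 0.0913) / true SE]
- Power with: Φ[0.256 / true SE − 1.960]

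**Example, ρ = 0.10.** True SE = 0.0913 × √0.90 = 0.0866, and the ratio is 1.054. Type I error = 2 × [1 − Φ(2.066)] = 3.9%. Power without is Φ(0.887) = 81.3%; with, Φ(0.993) = 84.0%.

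| Assumed share ρ | Reported SE / true SE | Type I error without | Power without | Power with | Points forgone |
|---|---|---|---|---|---|
| 0 | 1.000 | 5.0% | 80.0% | 80.0% | 0 |
| 0.05 | 1.026 | 4.4% | 80.6% | 82.0% | 1.4 |
| 0.10 | 1.054 | 3.9% | 81.3% | 84.0% | 2.7 |
| 0.20 | 1.118 | 2.8% | 82.7% | 88.0% | 5.3 |

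**Check by simulation.** 3,000 trials per setting, N = 120, blocks of 4 within equal strata, the 2×2 model with and without anaesthetist indicators, and no other covariates.

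| Anaesthetists | ρ | Type I error without / with | Power without / with |
|---|---|---|---|
| 5 | 0 | 4.7% / 4.8% | 79.0% / 79.0% |
| 5 | 0.05 | 4.5% / 5.1% | 79.8% / 81.1% |
| 5 | 0.10 | 4.0% / 4.8% | 81.9% / 84.1% |
| 5 | 0.20 | 3.0% / 4.4% | 82.6% / 86.4% |
| 10 | 0.10 | 4.0% / 5.1% | 80.9% / 83.4% |

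Monte Carlo error is about √(0.05 × 0.95/3000) = 0.4 points for type I error and √(0.8 × 0.2/3000) = 0.7 points for power. Direction and size agree with the formulas. The gap is somewhat smaller with 5 anaesthetists at ρ = 0.20 (3.8 points against 5.3).

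**The case against.** The strongest reply is that the plan does not exclude anaesthetist. The screening clause could admit it, and is more likely to when anaesthetist matters most. This is also a condensed article, and the coding of strata is often left to an analysis plan. The first part stands: a reader might infer that anaesthetist is left out of the analysis, and the text does not say so. The second part carries less weight here, because the article does not defer the model. It names six covariates and gives a selection rule for the rest, and that rule makes adjustment for the stratification factor depend on the data.

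Other parts of the case against also stand:
- The consequence is conditional. At a zero share nothing is lost. Named covariates such as theatre temperature and duration of surgery may absorb part of any anaesthetist difference, and the simulation did not include them. A raw share of 10% or 20% may therefore overstate the effect.
- A reader might infer that the trial loses power because of this. The figures do not show that. By the formulas, power without anaesthetist stays at or above 80% at the illustrative effect. What is forgone is a gain of a few points.
- A reader might infer that recovery time suffers most, since anaesthetic practice plausibly affects it. The article gives no recovery-time variance and no anaesthetist effect, so this cannot be supported.
- The 0.256°C effect is not in the article. At the stated 0.05°C, a 60 v 60 comparison has about 8% power before any gain from an anaesthetist term, and that shortfall has a different cause.

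**Conclusion.** The point holds in a limited form: the only stratification factor is not a pre-specified term in the ANCOVA, and its inclusion is left to a screen. That much is plain from the text.

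The size is uncertain because the share of variance due to anaesthetist is unknown. For residual shares of 0 to 20%, the standard error is 0 to 11.8% too wide, type I error runs from 5.0% down to 2.8%, and about 0 to 5 points of power are forgone. These figures assume a two-sided 5% test, complete and equal allocation within anaesthetist, and the illustrative 0.256°C main effect. The error is conservative and does not raise the false-positive rate. This is a modest matter of calibration and efficiency, worth correcting because the correction is simple and can be made before the data are seen.

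**What to change.** In the Statistical analysis section, state that anaesthetist is included in the ANCOVA for temperature, thermal comfort and recovery time, at both the interim and the final analysis, regardless of the bivariate screen. Enter it as a fixed effect. If some anaesthetists have few participants, use a random intercept instead, or pool them by a rule written down before unblinding. The article gives no basis for a particular cut-off, so the investigators should set one from their expected caseload.

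No new data are needed, since the anaesthetist must be known to randomise each participant. A fixed effect costs one degree of freedom per additional anaesthetist: 4 with 5 anaesthetists, 9 with 10, out of the 116 (120 − 4) left by the 2×2 model before other covariates. In the simulations with no anaesthetist effect, power was practically unchanged by adding the term (79.0% either way with 5 anaesthetists; 80.2% v 80.1% with 10).

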### Ethical considerations

The project has been approved by the hospital’s human research ethics committee. Informed consent will be obtained from all participants.

## Discussion

This trial is the first to rigorously evaluate the effect of preoperative warming and the use of warmed intraoperative irrigation solution on outcomes of particular interest to perioperative nurses, namely thermal comfort, and total recovery time. The factorial design of the trial enables a head-to-head comparison of the individual and cumulative effects of these two interventions which should provide valuable evidence to inform perioperative clinical practice.
